## **9. Follow-up Evaluations**

All patients will attend follow-up clinical evaluations at 1, 2, 3, 6, 9 and 12 months after the last treatment (Day 20). The follow up evaluations will be performed by the investigation team and will include the following procedures:

9.1 Record all evaluations on the CRF: disease status based on the less improved lesion (worse stage) in the case of a patient with more than one lesion. Registration of any additional therapy for leishmaniasis that the patient may have received. Take special note of the lesion size, inflammation, and re-epithelialization and score lesion evolution as detailed in section 8. Note presence and description of any additional lesions or mucosal lesions that may have appeared since previous visit.

9.2 Obtain photograph of the representative cutaneous lesion first photographed at baseline as described in section 8.2.7

9.3 Perform limited physical examination.

9.4 Record all adverse events since the last study visit.

## **10. Adverse Event Management.**

### **10.1 Adverse events**

An adverse event will be defined as any noxious, pathological or unintended change in anatomical, physiological or metabolic functions as indicated by physical signs, symptoms and/or laboratory changes occurring in any phase of the clinical trial, whether or not they are considered to be associated with the study drug. This includes an exacerbation of pre-existing conditions or events, intercurrent illnesses, drug interaction, or the significant worsening of the disease under investigation. Anticipated day to day fluctuations of pre-existing conditions, including the disease under study, that does not represent a clinically significant exacerbation or worsening of the condition, will not be considered adverse events.

All adverse events occurring after the start of the study (defined as when informed consent was obtained) are to be reported. This is regardless of whether or not they are considered to be drug-related. Adverse events (AEs) will be elicited by the

investigator asking the patient or the patient's parent or guardian a non-leading question such as "Do you/has your child felt different in any way since starting the new treatment or since the last assessment?" If the response is "Yes", the nature of the event, the date and time (where appropriate) of onset, the duration, maximum intensity (see below) and relationship to treatment are to be established (see below). Details of any changes to the dosage schedule or any corrective treatment are to be recorded on the appropriate pages of the CRF.

#### Assessment of Intensity/Severity

The assessment of intensity/severity will be based on the investigator's clinical judgment and categorized as follows:

**Mild:** An adverse event which is easily tolerated by the patient, causing minimal discomfort and not interfering with daily activities.

**Moderate:** An adverse event, which is sufficiently discomforting to interfere with normal daily activities.

**Severe:** An adverse event, which prevents normal daily activities.

#### Assessment of Causality

The investigator will use clinical judgment to determine the degree of certainty with which an adverse event is attributed to drug treatment. Alternative causes, such as natural history of the underlying diseases, concomitant therapy, etc are to be considered taking into account the known pharmacology of the drug, any previous reactions, literature reports and relationship to time of drug ingestion. Causality will be assessed using the following categories: not related, unlikely,

suspected (reasonable possibility) or probable. Patients with adverse events will be followed-up until the event disappears or the condition stabilizes.

If the treatment becomes intolerable to the patient for any reason (eg. Inflammatory response) this should be recorded as an AE and the cream application stopped.

### Serious Adverse Events

A serious adverse event will be defined as any event which is fatal, life threatening, disabling or incapacitating or results in hospitalization, prolonged hospital stay or is associated with congenital abnormality, cancer or overdose (either accidental or intentional). In addition, any experience which the investigator regards as serious or which suggests any significant hazard, contraindication, side effect or precaution that might be associated with the use of the drug will be reported as a serious event. Any serious adverse event occurring either during the study or within 30 days, of receiving the last dose of study medication, is to be reported by telephone to the study monitor within 24 hours. This will be followed by a full written summary containing copies of relevant hospital case records and autopsy reports where applicable.

As treatment is by topical application, over dosage is not anticipated. However, in the event of over dosage (error of dosage calculation or administration), this will be communicated to the Principal Investigator in Peru, [name], within 24 hours or as soon as possible thereafter. Details of any signs or symptoms and their management will be recorded on the CRF including details of any antidote(s) administered. As there are no specific antidotes available for the medications to be used in this study, patients will receive all supportive care needed at discretion of the treating physician and after consultation with the study coordinator above.

In a case of a Serious Adverse Event, the treatment code has to be opened by the investigators.

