## **6. Randomization, blinding and assignment of treatment.**

A randomization list from 1-80 will be generated by [name] at McGill University using a ratio of 1:1 to either the pentavalent antimony plus imiquimod arm or the pentavalent antimony plus placebo arm. The list will then be provided to a pharmacist, [name] at UPOCH who will be responsible for therapy preparation. This individual will not be involved in conducting the trials and therefore cannot administer the treatment or conduct patient evaluation(s). This list will contain the study I.D. numbers (1-80) and corresponding treatment assignments and remain completely blinded to the study investigators who will be treating and evaluating the patients.

Each patient will be assigned by the study doctor a study I.D. number from the above randomized list assigned in sequential order when he/she is enrolled in the trial. The study doctor at each site will ask to the study coordinator for the study ID number. The study ID number will be provide to the study coordinator by the pharmacist. This study ID number will be entered on the CRF for that patient. The nurse will then administer the treatment as detailed in section 7. The study doctor will carry out the evaluation and the nurse, doctor, and technician will remain blinded for the treatment and evaluation period.

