## 8. Evaluation of Clinical Response

The clinical response will be evaluated using standard descriptive criteria for assessing the size and severity of the cutaneous lesion. This will include, but will not be limited to: size of lesion, reduced ulceration, re-epithelialization, and inflammation reduction. The evaluation will be recorded by the study doctor and recorded on the **clinical report form (CRF)**.

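### Section 10 makes the investigators open the treatment code for every serious adverse event, while section 6 keeps the treating and evaluating staff blinded; the protocol does not reconcile the two or protect the causality judgement.

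*Protocol*

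**What the plan says.** The protocol describes a double-blind trial of 80 patients (section 3). On blinding, section 6 says two things. The randomization list is to "remain completely blinded to the study investigators who will be treating and evaluating the patients". And "the nurse, doctor, and technician will remain blinded for the treatment and evaluation period". The list is held by a pharmacist who takes no part in treating or evaluating patients.

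Section 10, under Serious Adverse Events, sets a different rule: "In a case of a Serious Adverse Event, the treatment code has to be opened by the investigators". It attaches no condition about suspected cause or need, and it names nobody outside the investigators to open the code. The definition of a serious event in the same section goes beyond the usual criteria. It adds "any experience which the investigator regards as serious or which suggests any significant hazard, contraindication, side effect or precaution" that might be linked to the drug.

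Three further statements show who makes the judgements that blinding is meant to protect:
- Section 8, on clinical response: "The evaluation will be recorded by the study doctor".
- Section 9, on months 1 to 12: "The follow up evaluations will be performed by the investigation team and will include the following procedures". Those procedures include scoring the lesion stage.
- Section 10, Assessment of Causality: "The investigator will use clinical judgment to determine the degree of certainty with which an adverse event is attributed to drug treatment".

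**The concern.** Once a serious event occurs, the staff have two instructions and no guidance on which prevails. If section 10 is followed as written, the investigators learn the patient's allocation, and section 6 uses that same word for the people who treat and evaluate. The protocol names no separate blinded assessor to take over from that point.

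Two judgements are at stake. Causality is a graded opinion in four categories, and knowing which cream was used can move it directly. Cure is a clinical reading of re-epithelialization and inflammation (sections 8.1 and 8.7), so it too depends on the assessor.

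The rule also opens the code when doing so tells the investigators little. All patients receive antimony openly (section 3), and section 1 names cardiopathy and pancreatitis among its toxicities. A hospital admission for either would oblige a code break that reveals only which cream the patient had.

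**Working it through.** There is no stated figure to reproduce: the point rests on no sample size, power or alpha value. It rests on comparing the text, with a small calculation of how far it could reach.

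**The rules side by side**

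| Question | Section 6 | Section 10 |
|---|---|---|
| Who? | Investigators who treat and evaluate; nurse, doctor, technician | The investigators |
| What? | Kept blinded | Must open the code |
| When? | Treatment and evaluation period | Any serious adverse event |
| Exception? | None stated | None stated |

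**Do the roles overlap?** Section 6 describes the study investigators as those who treat and evaluate. Section 8 gives the recording of response to the study doctor, section 9 gives follow-up scoring to the investigation team, and section 10 gives causality to the investigator. Section 3 lists one physician in the Lima team and two in the Cusco team. Overlap is therefore likely, and no sentence prevents it.

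**Is there an order of events?** Section 10 does not say whether causality is recorded before or after the code is opened.

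**Is the evaluation period long enough to matter?** It is not defined. Section 8 includes the analysis of response at 1 to 12 months (8.7), and section 9 calls the later visits evaluations, which points to month 12. On a narrow reading that ends with treatment, the conflict remains for events and causality judgements in the 20 treatment days.

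**Reach**

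- Inputs: 80 patients, 40 per arm (sections 3 and 15). The serious-event rate r is not in the protocol and is assumed here over a range.
- Weight of one unmasked patient in an arm's scoring: 1/40 = 2.5 percentage points.
- Expected number unmasked: 80r. Chance of at least one, treating patients as independent: 1 − (1 − r)^80.

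| Assumed r | Expected unmasked | Chance of at least one |
|---|---|---|
| 1% | 0.8 | 1 − 0.99^80 = 55% |
| 2% | 1.6 | 1 − 0.98^80 = 80% |
| 5% | 4 | 1 − 0.95^80 = 98% |
| 10% | 8 | 1 − 0.90^80 > 99.9% |

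So the rule is likely to be called on at least once even if serious events are uncommon, but for few patients. At 5% with an even split, two patients per arm (2/40 = 5 points of each arm) would be scored by someone who may know the allocation. That figure is the share of scoring exposed, not a bias in the cure difference.

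**The case against.** **Section 6 is the general rule and section 10 a specific exception.** This is a fair reading, and a reader who concludes that the two rules can never be followed together goes too far. What stands is that the exception is unconditional, section 6 does not refer to it, and nothing protects the later assessments.

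**The investigators who open the code may not be the doctors who score.** Section 11 contrasts the treating doctor with the investigators, and section 16.5 contrasts the attending physician with the Principal Investigators. So it cannot be stated as fact that the same people do both. But section 6 uses the term for those who treat and evaluate, and section 10 makes no distinction.

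**Emergency unblinding is legitimate.** Agreed. The fault is the automatic duty, not the possibility of opening a code.

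Two stronger readings are tempting, and the protocol does not support them:
- *Unmasking would fall mainly in the imiquimod arm, through local reactions.* The wide definition would allow a local reaction to be called serious. However, section 10 has an intolerable inflammatory response recorded as an adverse event with the cream stopped, and section 8.8 grades local reactions as tolerability. The toxicities named in section 1 belong to antimony, which both arms receive. A difference between arms is conjecture.
- *Several points of the cure difference are biased.* If 2 to 4 events all fell in one arm, 2/40 to 4/40, or 5 to 10 points, of that arm would be exposed to unmasked scoring. That is a worst case for exposure. An equal bias would need every one of those scores to change. Some of these patients might also be removed (section 11) and, with missing outcomes, left out of the primary analysis (section 15).

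**Conclusion.** The point holds as an unreconciled conflict with a practical consequence. Followed as written, section 10 unmasks investigators for every serious event under a wide definition, whatever the suspected cause, and the protocol does not keep that knowledge from those who judge causality and score stage. The causality assessment of serious events is the most exposed, because those are exactly the events for which the code is opened and no order is fixed.

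The effect on the cure comparison is probably small if serious events are rare: 2.5 percentage points of an arm's scoring per patient, against the 32-point difference on which section 15 bases the sample size. This rests on two assumptions. The investigators in section 10 include those who evaluate, which section 6 suggests but does not prove; and the event rate is low, on which the protocol is silent. The change should be made, but the point does not threaten the trial's main result.

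**What to change.** Reconcile sections 6 and 10 so that a serious adverse event does not automatically unmask the evaluating doctor, and refer from each section to the other. For any code that is opened, state that:

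1. Causality is recorded before the break.
2. The pharmacist, who already holds the list and neither treats nor evaluates, releases that single patient's allocation only.
3. The recipient is a named role that scores neither stage nor causality. This needs care because section 11 has adverse events reported by the investigators; without a separate recipient, the allocation could return to the assessors through the reporting route.
4. Each break is dated in the CRF and reported by arm.

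The circumstances in which the treating physician needs the allocation are for the sponsor to define; none is proposed here. An analysis that drops the unmasked patients is not recommended as part of this change, because it would exclude patients on the basis of an event after randomization.

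The cost is protocol wording, one CRF field, and a working arrangement that makes the pharmacist's list, held in Lima, reachable for the Cusco site within the 24-hour reporting time in section 10. The protocol does not describe such cover, so it may need a deputy or an on-call route.

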## **11. Patient Removal from Study**

Patients will be free to withdraw from the study at any time, for any reason, and without prejudice to further treatment. If the treating doctor determines that the clinical situation is worsening to an extent greater than a) one would expect from the natural history of the disease, or b) the range of clinical progression seen in previous cohorts of patients with similar initial clinical findings, he/she may elect to remove the patient from the clinical trial and to initiate treatment with the best medical regimen available.

Patients may also be removed from the study by the investigators, if necessary, in the event of a severe adverse event, pregnancy, or if the patient develops a concurrent illness which would preclude continuation in the study. Patients who are withdrawn from the study due to concurrent illness will be counseled by the investigators to receive the appropriate care. Patients who are removed from the study will undergo medical evaluations and will be followed for toxicity as closely as possible. Any patient who discontinues, regardless of the reason, will not be allowed to re-enroll in this study. The CRF will include reasons for withdrawal and any necessary treatment. Adverse events will be reported by the investigators and to the Ethics committee at UPOCH and McGill University.

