#### **8.4 Day 10 evaluation and treatment procedures**

- 8.4.1 Record concomitant medications on the CRF.
- 8.4.2 Perform a complete physical examination (study doctor).
- 8.4.3 Assess vital signs prior to treatment application.
- 8.4.4 Assess the active cutaneous lesions identified during the screening/baseline visit. Note presence and description of any additional lesions that may have appeared since previous visit. Stop therapy if a mucosal lesion has developed
- 8.4.5 Record adverse events occurring since the last evaluation.
- 8.4.6 Take a drawing of each lesion using a plastic sheet, drawing the borders of each lesion.
- 8.4.7 Obtain photograph of the representative cutaneous lesion first photographed at baseline following the same procedures of section 8.2.7
- 8.4.8 Collect blood for safety evaluations as follows (study technician):  
Approximately 2.5 ml anticoagulated (EDTA) whole blood for CBC, white cell differential and platelet count.  
  
Approximately 8.5 ml whole blood into serum separator tube (SST) for serum chemistry testing. Chemistries to include: ALT, AST, total bilirubin, alkaline phosphatase, pancreatic amylase, glucose and creatinine.
- 8.4.9 Electrocardiogram: Only if a cardiovascular condition should be monitored.

- 8.4.10 Administer treatment to the patient as described in Section 7 as long as there are no severe adverse events as detailed in section 10.1 .

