#### **8.7 Analysis of the response to therapy at 1, 2, 3, 6, 9, 12 months of follow-up:**

Improvement: Significant reduction in the size of the lesion at the time of evaluation (Stages M1-M3) compared to baseline.

Cure: Complete re-epithelialization of the lesion without inflammation (Stage M4).

Failure: Any one of the following or combined options

Stage MO at 1 month of follow up after the treatment

Stage M1 at 3 months of follow up after the treatment

Regression of the clinical stage to a lower stage or development of a new lesion.

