**15. Statistical Considerations**

The randomized clinical trial study design uses a rigorous methodology to evaluate the clinical research questions posed in this proposal. The sample size has been calculated based on estimates from previous published data results and will ensure adequate statistical power while maintaining efficiency. Minimal loss to follow-up is expected (<10%). The primary analyses will be conducted excluding patients with missing outcomes. Intention-to-treat analysis will also be performed (ie. including all patients randomized).

Descriptive statistics (means  $\pm$  standard deviation (SD), proportions and, when required, medians and interquartile ranges) will be performed to compare socio-demographic, clinical and epidemiological characteristics of patients at baseline between experimental and control groups. These characteristics include: age, sex, region of residency and education/occupation, among others. Proportions of patients cured at each of the follow up dates will be assessed. Proportions will be compared between the two groups using chi-square tests. Means derived from continuous variables will be compared using t tests or non-parametric tests, as appropriate.

Time-to-cure will be compared between the two groups using Kaplan-Meier curves and crude rates of cure will be calculated by person-years. For comparison purposes, we will assume that cure occurred at the time of the visit for cured patients. In a randomized clinical trial, we expect to find no differences in patient characteristics

between the two groups. However, when sample sizes are small, it will likely be necessary to adjust for slight imbalances in independent variables between the two groups. Cox proportional-hazard models will be constructed to determine the effect of treatment on time-to-cure, adjusting for patients' baseline characteristics. Results will be expressed in terms of hazard ratios and 95% confidence intervals. The proportional hazard assumption will be examined using graphical methods and the proportional hazard test in SAS PHGLM. Secondary analyses will be conducted in a similar manner, assuming that all those who were lost to follow-up were cured only at the end of the 12 month follow-up period.

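### Section 11 makes a treatment switch for worsening a removal from the trial, so a patient whose lesion enlarges before month 1 can be left out of the primary analysis instead of counting as a failure

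*Protocol*

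**What the plan says.** - **Removal (section 11).** When worsening exceeds what the natural history or earlier cohorts would suggest, the protocol says of the treating doctor that "he/she may elect to remove the patient from the clinical trial and to initiate treatment with the best medical regimen available". Afterwards, "Patients who are removed from the study will undergo medical evaluations and will be followed for toxicity as closely as possible". No M0–M4 staging and no month 1–12 visits are named for these patients. The CRF records the reason for withdrawal and any necessary treatment.
- **Outcome (sections 8.1 and 8.7).** M0 covers a lesion that is unchanged or larger than before treatment. Response is classified at months 1, 2, 3, 6, 9 and 12. The earliest dated Failure criterion is "Stage MO at 1 month of follow up after the treatment". One criterion carries no date: "Regression of the clinical stage to a lower stage or development of a new lesion". Neither removal nor a switch of treatment is listed as Failure.
- **Analysis (section 15).** "The primary analyses will be conducted excluding patients with missing outcomes". An intention-to-treat analysis of all randomized patients is added, without saying how removed patients are handled. For time to cure, "we will assume that cure occurred at the time of the visit for cured patients". Secondary analyses take patients lost to follow-up as cured at month 12.
- **Follow-up (section 9).** "All patients will attend follow-up clinical evaluations at 1, 2, 3, 6, 9 and 12 months", and any additional leishmaniasis therapy is recorded.
- **Medication (section 12).** A medication leads to discontinuation only if it would interfere with interpreting the results or be unsafe for the patient.

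**The concern.** Starting another regimen is a clinical decision. Leaving the trial is a decision about data. Section 11 makes them one act, and the trigger is worsening, which is the opposite of the endpoint. If the removed patient then has no classified outcome, the exclusion in section 15 is related to outcome: it takes uncured patients out of the denominator and raises the cure proportion of the arm they leave. The comparison between arms is distorted to the extent that removal differs by arm. With 40 patients per arm, a handful of such exclusions is visible in the result.

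**Working it through.** **1. Can such a patient have no outcome?** Month 1 is counted from Day 20, so the first classification falls about 20 + 30 = 50 days after Day 1. Take a patient removed inside that window:

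- The lesion has enlarged and never improved: the stage is already M0, the lowest, so it cannot regress.
- There is no new lesion: the undated criterion is not met.
- Month 1 has not been reached: the M0-at-month-1 criterion is not met.
- No later staging visit is named for removed patients: nothing fills the gap afterwards.

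The outcome can therefore be missing, and section 15 excludes the patient from the primary analyses.

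**2. The plan's own figure.** Inputs from section 15: 40 per arm, 35% vs 67% cured, hazard ratio 2.6, 80% power by log-rank. Alpha is not stated; two-sided 0.05 is assumed.

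- Implied hazard ratio: ln(1 − 0.67)/ln(1 − 0.35) = 2.57.
- Expected cures: 40 × 0.35 + 40 × 0.67 = 40.8.
- Freedman power: Φ(√40.8 × 1.57/3.57 − 1.96) = 80.3%, or 81.0% with a hazard ratio of 2.6.

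The stated power reproduces and is not in dispute.

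**3. Effect of excluding uncured patients.** At the planning values, 14 control and 26.8 experimental patients are cured. Excluding k uncured patients gives 14/(40 − k) or 26.8/(40 − k). One exclusion raises control to 14/39 = 35.9% or experimental to 26.8/39 = 68.7%. The numbers removed are assumptions, because the documents give none.

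| Uncured patients excluded | Control | Experimental | Difference (points) | Implied hazard ratio |
|---|---|---|---|---|
| None (kept as Failure) | 35.0% | 67.0% | 32.0 | 2.57 |
| 10% of uncured, both arms (3.9 of 80) | 37.4% | 69.3% | 31.9 | 2.52 |
| 20% of uncured, both arms (7.8 of 80) | 40.2% | 71.7% | 31.5 | 2.46 |
| 2, control only | 36.8% | 67.0% | 30.2 | 2.41 |
| 4, control only | 38.9% | 67.0% | 28.1 | 2.25 |
| 2, experimental only | 35.0% | 70.5% | 35.5 | 2.84 |
| 4, experimental only | 35.0% | 74.4% | 39.4 | 3.17 |

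The equal-share rows use 0.35/(1 − 0.65f) and 0.67/(1 − 0.33f), with f = 0.10 or 0.20. Equal numbers are not the same as equal shares: 4 from each arm gives (26.8 − 14)/36 = 35.6 points.

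**4. A borderline result.** With 14/40 vs 21/40 cured, the chi-square p-value is 0.115 when removed patients count as failures. It is 0.042 when 4 uncured experimental patients are excluded.

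**The case against.** Several counter-arguments narrow the point.

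- **Mucosal or new lesions.** At Day 10 the protocol says "Stop therapy if a mucosal lesion has developed", and a reader might infer that even this event would yield no outcome. The documents do not support that. The undated criterion on a new lesion plausibly makes it a Failure, although the heading of 8.7 refers to follow-up visits. Section 8.4 also stops therapy there and does not say that the patient leaves the trial. The clear gap is enlargement alone.
- **Other follow-up.** Section 10 counts significant worsening of the disease as an adverse event and follows adverse events until they resolve or stabilize. Removed patients are therefore not abandoned, but no staging is required. Section 9 speaks of all patients, yet section 11 sets a different follow-up for removed ones, and section 9 does not say that it prevails.
- **Time to cure.** A reader might infer that these patients are necessarily lost from the Kaplan-Meier, log-rank and Cox analyses. That holds only if they are censored at removal before the first dated cures, which the protocol does not state. If they were instead treated as lost to follow-up, the secondary analyses would keep them at risk but record them as cured at month 12, which is also wrong for a failure.
- **This belongs in the SAP.** Partly right. Classifying these patients as Failure needs no later staging, and the CRF already holds the reason for removal. However, the protocol itself states both the removal and the primary exclusion, and an SAP cannot recover visits that were not made if an analysis uses observed later status.
- **Intention-to-treat.** This analysis is additional and does not undo the stated primary exclusion.
- **Rarity and balance.** Removal is discretionary, needs unexpected worsening within about 50 days, and is decided by doctors who are normally blinded. This stands, and it limits the expected size.

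**Conclusion.** The point holds in a narrow form. As written, a patient removed before month 1 for an enlarging M0 lesion without a new lesion can be excluded from the primary analyses although in substance a treatment failure. Size and direction are unknown. The effect on the difference is close to nil if equal shares of uncured patients are removed from both arms. The difference is about 28 to 39 points instead of 32 if 4 uncured patients leave one arm only. These figures assume the planning cure rates, that every removed patient is uncured, and that the exclusion is applied as stated. A reader might infer a bias in favour of imiquimod. Nothing in the documents supports a direction, nor a reason for removal to occur in one arm only. This is a cheap improvement, not a flaw that undermines the design.

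**What to change.** - **Section 11:** let the doctor stop study treatment and start other anti-leishmanial treatment for worsening without removing the patient from the trial. Keep the patient on the section 9 visits unless consent is withdrawn, and record drug and date. The clinical trigger and the choice of regimen stay with the investigators.
- **Sections 8.7 and 15:** count removal or switch for worsening at any time after Day 1 as Failure (not cured) in the primary and intention-to-treat analyses, whatever healing follows. In the time-to-cure analyses keep the patient at risk as not cured to month 12. In the secondary analyses do not treat the patient as lost to follow-up and so cured at month 12.
- **Section 12:** state that anti-leishmanial rescue therapy alone does not end follow-up, and keep the existing exception for patient safety.

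**Cost:** protocol wording only, since the visits are already planned. Some patients would attend visits they would otherwise skip. The doctor's decision becomes part of the outcome; that decision is normally blinded, except where the code is opened for a serious adverse event. Counting a switch as Failure is one legitimate choice among several, but it follows the sense of 8.7 and avoids the outcome-related exclusion.
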